For analysis of patient-directed discharge, study entry will be at hospital admission. For analysis of readmission, study entry will be at discharge, such that patients who died during the index admission are excluded. We will use a mixed (hierarchical) linear model in which the dependent variable is a binary indicator of the outcome, and independent variables are an interaction term between two binary outcomes: time (i.e., before/after iHOST implementation) and iHOST site or control; a random intercept for the hospital site; and patient-level confounders/covariates. This approach to modelling is known as a ‘linear probability model’, and we have selected it to allow estimation of absolute difference in the risk of outcomes. Confounders will be age, sex, season, primary cause of admission, number of comorbidities, proportion of patients at the hospital who have COVID-19. We will fit the model using a restricted maximum likelihood method implemented in the
R package
lme4
^
31
^. The effect of iHOST will be interpreted from the interaction between time and the control/intervention indicator. Definitions of study variables are included in Extended Data
^
32
^.

**
*Baseline data analysis.*
** We extracted data from Hospital Episode Statistics for the calendar year 2021 to estimate the number of eligible patients and understand their characteristics. The results are summarised in
Table 1. Hospitals are anonymised.

**Table 1. T1:** Number and characteristics of patients with recent diagnoses of opioid dependence in the calendar year 2021, based on preliminary analysis of Hospital Episode Statistics.

Site	Number of patients	Patient-directed discharge N (%)	28-day readmission N (%)	Age (IQR)	Male N (%)	5+ comorbidities N (%)	% patients at hospital with COVID-19
iHOST sites							
A	349	70 (20.1)	101 (28.9)	46 (36-54)	244 (69.9)	143 (41.0)	10.1
B	662	149 (22.5)	214 (32.3)	43 (38-47)	489 (73.9)	195 (29.5)	6.9
C	624	116 (18.6)	148 (23.7)	43 (37-50)	392 (62.8)	182 (29.2)	4.8
Control hospitals							
All	24604	4048 (16.5)	7001 (28.5)	43 (37-50)	16425 (66.8)	6718 (27.3)	7.9
1	893	61 (6.8)	322 (36.1)	42 (35-49)	535 (59.9)	97 (10.9)	6.1
2	818	102 (12.5)	156 (19.1)	40 (35-47)	584 (71.4)	138 (16.9)	8.3
3	728	103 (14.1)	183 (25.1)	45 (37-52)	458 (62.9)	134 (18.4)	9.0
4	732	191 (26.1)	265 (36.2)	45 (38-50)	533 (72.8)	208 (28.4)	6.7
5	739	92 (12.4)	249 (33.7)	43 (37-50)	445 (60.2)	185 (25.0)	5.8
Etc …							

**
*Power.*

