** To estimate power, we simulated the study assuming that iHOST reduces the risk of each outcome by 5 percentage points (for example from 20% to 15%). For the “pre iHOST” data, we used the calendar year 2021 (summarised in
Table 2). For the "post iHOST” data, we used same dataset; but with outcomes randomly generated where the risk of each outcome was the hospital-specific risk from 2021, reduced by 5 percentage points for the iHOST sites. An example of a single simulation is shown in
Figure 3. We repeated this simulation 1,000 times and calculated the proportion of simulations in which a significant result was found (ie. p <0.05). This suggested good power to detect a risk reduction of 5 percentage points when results from the three hospitals are pooled, but low power at individual sites. Code for the power analysis is available at
https://github.com/[name]/ihost/tree/main/power.

**Table 2. T2:** Power of the iHOST study to detect an absolute reduction in outcomes of five percentage points.

	Patient-directed discharge	28-day emergency readmission
Site A	0.475	0.228
Site B	0.839	0.442
Site C	0.837	0.376
Pooled effect	>0.999	0.921

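### As described, the power simulation randomises only the post-period and holds the 2021 pre-period fixed, so most powers in Table 2 are distorted; good pooled power is expected to survive

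*Protocol article*

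**What the plan says.** The Power paragraph (protocol article, Difference-in-difference study) states the assumed effect: "we simulated the study assuming that iHOST reduces the risk of each outcome by 5 percentage points". For the period before iHOST, "data, we used the calendar year 2021". For the period after, "we used same dataset; but with outcomes randomly generated where the risk of each outcome was the hospital-specific risk from 2021", with 5 points taken off at the iHOST sites. Then: "We repeated this simulation 1,000 times and calculated the proportion of simulations in which a significant result was found (ie. p <0.05"). Nothing says that the pre-period outcomes were redrawn.

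Table 2 gives power for patient-directed discharge and 28-day readmission as 0.475 and 0.228 at Site A, 0.839 and 0.442 at Site B, 0.837 and 0.376 at Site C, and >0.999 and 0.921 pooled. The text summarises this as good pooled power "but low power at individual sites".

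The planned analysis is a linear probability model: "We will use a mixed (hierarchical) linear model in which the dependent variable is a binary indicator of the outcome". The effect is read from the period-by-group interaction, with a random hospital intercept, and each hospital is analysed separately. Under Population, the study window is the 12 months either side of each launch. The launch dates under The intervention are November 2022 and January 2024.

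**The concern.** A difference-in-difference estimate carries sampling error from both periods. In the simulation as described, the pre-period is the same data in every run, and the post-period is drawn around exactly the rates observed in that data. Only the post-period varies. The fitted model does not know this, so its standard error still counts both years. The simulated estimates are then much less spread out than the test assumes.

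The error has no single direction. The chance that the estimate exceeds 1.96 standard errors moves towards 0 or 1, away from 50%. Powers above 50% come out too high and powers below 50% too low.

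At stake is the credibility of Table 2. The site-level figures describe the analysis the protocol specifies, and readers will judge site results against them. The table also conflicts with its own summary, which calls individual-site power low although discharge power at B and C is given as 0.839 and 0.837.

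**Working it through.** **Inputs (Table 1).** Discharge and readmission counts: Site A n = 349, 70 and 101; Site B n = 662, 149 and 214; Site C n = 624, 116 and 148; controls n = 24,604, 4,048 and 7,001. Effect 0.05. The test is assumed two-sided at 0.05, because the article does not state sidedness. No covariates are used. The same patients appear in both years, so hospital intercepts cancel from the contrast.

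**Formulas.**
- Fixed pre-period: Var = p1(1−p1)/n + pc(1−pc)/N.
- Both years redrawn: Var = [p0(1−p0) + p1(1−p1)]/n + 2pc(1−pc)/N.
- Model SE = sqrt[s²(2/n + 2/N)], with s² the pooled residual variance.
- Power ≈ Φ[(0.05 − 1.96 × SE)/SD].

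**Site B discharge.** p0 = 149/662 = 0.225, p1 = 0.175, pc = 4,048/24,604 = 0.165.
- Site variance: pre 2.635e-4, post 2.182e-4. Control variance per year: 0.056e-4.
- SD with the pre-period fixed = sqrt(2.238e-4) = 0.0150.
- SD with both years redrawn = sqrt(4.928e-4) = 0.0222.
- Variance ratio = 2.238/4.928 = 0.45.
- s² = 0.138, so SE = sqrt[0.138 × (2/662 + 2/24,604)] = 0.0207.
- Power, fixed: Φ[(0.0500 − 0.0406)/0.0150] = 0.74. Redrawn: Φ[(0.0500 − 0.0406)/0.0222] = 0.66 to 0.67.

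Across the eight cells the variance ratio is 0.44 to 0.48, so 52–56% of the variance is removed.

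**Check under no effect.** The fixed scheme rejects in 0.3% to 1.3% of runs. With both years redrawn the rate is 3.8% to 7.9%, around the nominal 5%.

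**All cells.** The middle columns come from 200,000 draws per cell. The last column does not rely on the reconstruction's absolute levels. It rescales the stated power as Φ[Φ⁻¹(stated) × SD fixed/SD redrawn]; for Site B discharge this is Φ(0.990 × 0.674) = 0.75. For pooled discharge, >0.999 is taken as 0.999.

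| Cell | Table 2 | Pre fixed | Both redrawn | Change (points) | Table 2 rescaled |
|---|---|---|---|---|---|
| Discharge A | 0.475 | 0.396 | 0.426 | +3.0 | 0.48 |
| Discharge B | 0.839 | 0.737 | 0.665 | −7.2 | 0.75 |
| Discharge C | 0.837 | 0.730 | 0.654 | −7.6 | 0.74 |
| Discharge pooled | >0.999 | 0.994 | 0.958 | −3.6 | 0.98 |
| Readmission A | 0.228 | 0.226 | 0.301 | +7.5 | 0.30 |
| Readmission B | 0.442 | 0.518 | 0.511 | −0.7 | 0.46 |
| Readmission C | 0.376 | 0.490 | 0.491 | +0.1 | 0.42 |
| Readmission pooled | 0.921 | 0.952 | 0.874 | −7.8 | 0.83 |

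**Does this reproduce Table 2?** Not exactly. The fixed scheme comes within 2 points in two of eight cells (pooled discharge and readmission A); the redrawn scheme does so in none. Only 5 of the 50 control hospitals are listed, and the covariates and code are not in the article. With one free offset in the effect per outcome, the fixed scheme fits Table 2 to within 1.2 points for discharge and 4.0 for readmission, against 5.8 and 7.7 for the redrawn scheme. This agrees with the article's description that only the post-period was randomised.

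**The case against.** **The conclusion does not change.** Pooled power stays good on either route, and the corrected site figures fit the statement of low site power better than Table 2 does. No recruitment target depends on these cells, because the study takes all eligible admissions in fixed windows. This stands, and it is why the point is a should-fix.

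**The whole gap from Table 2 is not this flaw.** A reader might set the stated 0.839 at Site B against the redrawn 0.665 and blame the simulation for about 17 points. That is not supported. Within one reconstruction the flaw accounts for 7.2 points. The other 10 (0.839 against 0.737) are failure to reproduce the table, whose cause cannot be seen from the article. Covariate adjustment cannot be ruled out as part of the discharge gap.

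**Site-level readmission power is not shown to be understated throughout.** The reconstruction supports this at Site A only. At B and C it moves by less than 1 point. Rescaling would raise them by about 2 and 4 points, but only because the stated values lie below 50%, a feature the reconstruction does not reproduce at C or B.

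**The 2021 data are known, so holding them fixed may seem legitimate.** This does not stand. The actual pre-periods fall almost wholly outside 2021; only the November 2022 launch can reach back into its last two months. Even for 2021 itself, centring the post-period on the observed rates treats that year's sampling noise as the true risk.

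**The code is linked but was not available here.** If it does redraw the pre-period, the Power paragraph misdescribes it and still needs correcting.

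**Conclusion.** The concern holds for the simulation as the article describes it. Holding the pre-period fixed removes about half the variance of the estimate while the test allows for all of it, so Table 2 does not give the power of the planned analysis.

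Indicative corrected values, taking both routes together:
- discharge at B and C about 0.65–0.75, where about 0.84 is stated;
- pooled readmission about 0.83–0.87, where 0.921 is stated;
- pooled discharge about 0.96–0.98, where >0.999 is stated;
- Site A readmission about 0.30, where 0.228 is stated.

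Site A discharge rises by 3 points at most.

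These ranges assume a two-sided test, no covariates and no hospital-by-period variation. They are not replacement figures, since Table 2 could not be reproduced. A reader might infer that the study is underpowered overall; the figures do not support that for the 5-point effect assumed. The text and table do disagree on individual sites, but that is a wording matter which correction would largely settle. Severity: should-fix.

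**What to change.** Rerun the existing power code with outcomes drawn at random in both periods from the hospital-specific risks. Check that it rejects in about 5% of runs when the effect is set to zero. Replace Table 2 with the result, state whether the test is two-sided, and amend the description of the pre-iHOST data to match. Reword the sentence on individual sites so that it agrees with the new table for each outcome. If the code already redraws both periods, correct the description instead.

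The cost is one rerun, one table and two or three sentences. Discharge power at B and C and both pooled figures are expected to be less favourable; Site A readmission should improve. Design and data collection are unaffected. Adding hospital-by-period variation or power for smaller effects would be a separate request and is not needed to correct this error.

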**Figure 3. f3:**
[figure not shown]
Example results from a single simulation of the difference-in-difference study.

### OST process measures

Participating hospitals will use local clinical data to report measures of the quality of OST provision (‘process measures’). We have worked with information specialists and clinicians at University College London Hospital NHS Foundation Trust to develop the following measures:

1. The number of patients administered methadone. Most patients provided with OST in acute hospitals in the UK are given methadone; and additionally, methadone is rarely given for other indications. Therefore, it is a useful indicator of the quantity of OST provided; while avoiding the need to consider the indication and formulation.2. Duration between decision to admit and administration of methadone, reported as (a) the proportion that is 24 hours or greater; and (b) the median and interquartile range.3. The dose, defined as (a) the proportion of patients administered at least 20mg of methadone in one 24-hour period; reported as a proportion of patients who are administered methadone and admitted for at least 24 hours, and (b) the mean and distribution of administered doses across 24-hour intervals following admission.4. The proportion of potentially eligible patients who are provided with OST, defined as the proportion of inpatients with a discharge diagnosis of ICD-10 F11 (‘opioid related disorders’) who were administered methadone or buprenorphine during their admission.5. The proportion of patients who are potentially eligible for OST who have a patient-directed discharge, defined as the proportion of inpatient admissions with discharge diagnosis of ICD-10 F11 (‘opioid related disorders’) that end in patient-directed discharge.6. Possible OST-associated overdoses, defined as inpatients who are administered naloxone after an administration of methadone or buprenorphine.

Depending on the feasibility of extracting these data, each iHOST site will calculate each measure for quarterly periods (i.e., every three months) for time periods before and during iHOST implementation. The sites will nominate a group of staff (for example medical staff, pharmacists, and information specialists) to review the indicators every three months. We will also do an uncontrolled before/after analysis to test if the indicators change after implementation of iHOST.

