### The intervention

We will develop and evaluate an intervention (iHOST) to improve OST in acute hospital settings. iHOST will be implemented at three acute hospitals in England: University College London Hospital, St. James University Hospital Leeds, and Royal Stoke University Hospital. The project will be developed in partnership with local drug treatment services. The intervention primarily aims to improve continuation of OST from community to hospital settings but will also inform OST initiation and discharge planning for patients who were not already in receipt of community-based OST. The programme phases are shown in
Figure 1, and launch dates are currently anticipated to be:

University College London Hospital: November 2022 (already launched at the time of publication)St James University Hospital Leeds: January 2024Royal Stoke University Hospital: January 2024

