**Health economic study.** We may not be able to accurately estimate the difference in methadone prescriptions. In many cases methadone may have been prescribed without the iHOST protocol, but having the protocol in place may mean that it is prescribed more quickly. We will do sensitivity analysis around this, assuming ranges in counterfactual prescription rates without the iHOST protocol in place. Costs included in the economic evaluation will be specific to sites where the study is operating and may not be generalisable to other settings or implementation of iHOST at large scale. We are unable to do any modelling of long-term outcomes, and therefore cost and effect estimates may not include important future events.

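### The overdose process measure has no denominator, so its before/after test moves with the number of patients given OST as well as with risk

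*Protocol article*

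**What the plan says.** All of this is in the Protocol article, mainly under OST process measures.

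- Measure 6 is "Possible OST-associated overdoses, defined as inpatients who are administered naloxone after an administration of methadone or buprenorphine". No denominator follows. Measures 3(a), 4 and 5 in the same list are each written as a proportion of a named group.
- Measure 2 is "Duration between decision to admit and administration of methadone, reported as (a) the proportion that is 24 hours or greater", together with a median and interquartile range.
- Measure 1 is "The number of patients administered methadone". Measure 4 is "The proportion of potentially eligible patients who are provided with OST", defined among inpatients with an F11 discharge diagnosis who received methadone or buprenorphine.
- If the data can be extracted, "each iHOST site will calculate each measure for quarterly periods (i.e., every three months) for time periods before and during iHOST implementation". Site staff review the results each quarter.
- The article then states: "We will also do an uncontrolled before/after analysis to test if the indicators change after implementation of iHOST".

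Two other statements bear on how many patients will be treated. The section on the intervention says that iHOST "will also inform OST initiation and discharge planning for patients who were not already in receipt of community-based OST". The health economic limitation in the Discussion says: "In many cases methadone may have been prescribed without the iHOST protocol". The limitation on process measures in the Discussion presents them as aids to local learning. It warns that they do not estimate impact robustly, and it names changing use of OST as another reason why they may move.

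**The concern.** A count of patients given naloxone after OST is the number given OST multiplied by the risk per treated patient. iHOST may change both. A before/after test on the count cannot separate a pathway that has become less safe from one that reaches more patients at the same risk. It can also miss a pathway that has become safer while growing. The measure is meant to show sites something about the safety of OST in their setting, and without a denominator it does that poorly.

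Measure 2 raises a related question. Patients who never received methadone, including those who left before a first dose, have no value. If iHOST brings in recipients whose delays differ from those of earlier recipients, the before/after comparison mixes a change in speed with a change in who is measured.

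**Working it through.** The article gives no rate, number treated, significance level or power for the process measures, so there is no figure of its own to reproduce. The power table belongs to the difference-in-difference study and plays no part here. Every input below is an assumption chosen for illustration.

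**Measure 6: direction.** Let k be the ratio of patients treated after to before, over periods of equal length, and q the ratio of risk per treated patient. The expected count ratio is k × q.

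- Risk unchanged (q = 1): the ratio is k, so 25% more patients treated gives 25% more events and twice as many gives twice the events.
- Risk down 20%, 25% more treated: 0.80 × 1.25 = 1.00. The improvement disappears.
- Risk down 20%, 50% more treated: 0.80 × 1.50 = 1.20. An improvement looks like harm.

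**Measure 6: how often a test would be misled.** Poisson counts were simulated (20,000 runs per row) with the true risk per treated patient unchanged. The test was an exact conditional binomial test, two-sided at an assumed 0.05. Without a denominator, the after-period share of events is tested against 1/2. With a denominator, it is tested against n₁/(n₀ + n₁), where n₀ and n₁ are the numbers treated before and after. The entries are the probability of a significant apparent increase.

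| Treated before | Risk | k | Expected count | Tested as count | Tested per treated |
|---|---|---|---|---|---|
| 200 | 2% | 1.25 | 4 → 5 | 2.3% | 0.8% |
| 200 | 2% | 1.5 | 4 → 6 | 4.6% | 0.8% |
| 200 | 2% | 2.0 | 4 → 8 | 13.4% | 0.7% |
| 200 | 5% | 1.25 | 10 → 12.5 | 5.0% | 1.6% |
| 200 | 5% | 1.5 | 10 → 15 | 12.0% | 1.5% |
| 200 | 5% | 2.0 | 10 → 20 | 37.2% | 1.3% |
| 400 | 2% | 1.25 | 8 → 10 | 4.0% | 1.2% |
| 400 | 2% | 1.5 | 8 → 12 | 9.6% | 1.3% |
| 400 | 2% | 2.0 | 8 → 16 | 29.4% | 1.3% |
| 400 | 5% | 1.25 | 20 → 25 | 8.7% | 1.7% |
| 400 | 5% | 1.5 | 20 → 30 | 25.1% | 1.7% |
| 400 | 5% | 2.0 | 20 → 40 | 70.2% | 1.7% |

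The nominal rate in this direction is 2.5%. The per-treated test stays below it throughout. The count ranges from about nominal to 70%, depending entirely on the assumptions.

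**Measure 2.** Assume 100 eligible inpatients. Before, 50 are treated and 10 of them are late (24 hours or more): 10/50 = 20% late, and 40/100 are treated in time. After, 50 similar patients have 5 late starts, and 25 further patients are treated, of whom L are late. The recipients-only figure is (5 + L)/75.

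- L = 3: 8/75 = 10.7%. In time among all eligible: (45 + 22)/100 = 67%.
- L = 10: 15/75 = 20%. In time: 60%. The gain is hidden.
- L = 15: 20/75 = 26.7%. In time: 55%. The gain looks like a loss.

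The figure looks worse only when (5 + L)/75 exceeds 0.20, that is when L exceeds 10. More than 40% of the new recipients must then be late, against 5/50 = 10% of the others. If the new recipients are late as often as the others (L = 2.5), the figure is 7.5/75 = 10% and nothing is distorted.

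**The case against.** The strongest reply is that the wording of measure 6 defines an event and not a reporting scale. Measure 1 says explicitly that it is a number and measure 6 does not, and a condensed article may leave the scale to the full protocol or analysis plan. That has some force. Against it, the same list states denominators for three other measures, the article commits to testing the indicators, and the Extended Data it describes cover only the difference-in-difference study. Even on the generous reading, the definition needs completing.

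The second reply is disclosure. The Discussion already says that these measures do not estimate impact robustly and that changing use of OST can move them. For measure 2 this covers much of the ground. For measure 6 it neither supplies a denominator nor withdraws the test. Measures 1 and 4 let a reader correct in part for volume, but measure 1 counts methadone only and measure 4 covers F11-coded inpatients only. Neither is the denominator of measure 6.

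Third, the main aim is continuation of OST, and the article expects that many patients would have had methadone anyway. If iHOST mainly changes speed, the number treated moves little, measure 6 is distorted little, and measure 2 does its job. This stands, and it limits the likely size of the problem.

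A reader might go further in three ways that the article does not support:

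- **That measure 2 shifts mechanically.** It shifts only if new recipients have different delays, and the direction is open. This is selection.
- **That a misleading count would drive safety decisions.** The Safety section relies on governance processes and review of individual events. It attaches no decision or threshold to measure 6, and the total count is itself a legitimate safety figure.
- **That measure 2(a) should be replaced by a proportion of all F11 inpatients.** That proportion merges coverage with speed. It also counts as failures those who may not need OST and those who leave before 24 hours.

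**Conclusion.** The point holds for measure 6. As written it has no denominator, and the before/after test would respond to the number of patients given OST as well as to risk. At constant risk the expected count rises in proportion to the number treated, and a 20% fall in risk is cancelled by a 25% rise in numbers. This rests on one assumption, that iHOST increases the number given OST. The article makes that plausible by covering initiation, but gives no figure for it.

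For measure 2 the point is narrower. The measure is conditional on receiving methadone, so a before/after change may reflect a changed mix of recipients, in either direction. The article discloses part of this.

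The size of any false signal cannot be derived from the article; the simulated probabilities only illustrate a range. The primary outcomes, patient-directed discharge and 28-day emergency readmission, come from the controlled study and are not touched.

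**What to change.** **Measure 6.** Define, report and test it as the number of inpatients given naloxone after methadone or buprenorphine per 100 inpatients administered either drug in the same period, with an exact confidence interval. Keep the count alongside. The cost is one further extraction, the number of all inpatients administered methadone or buprenorphine, which measures 1 and 4 supply only in part.

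**Measure 2.** Keep it as defined. Where the data allow, add beside it the proportion of F11 inpatients given methadone within 24 hours of the decision to admit. State that this figure combines coverage with speed and that its denominator includes patients who may not need OST or who leave before 24 hours. Restricting it to methadone avoids asking for buprenorphine timing, which the article does not list. The cost is linking methadone timing to F11 coding, subject to the feasibility condition that the article already sets.
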